### Patient and public involvement {11}

Patients or members of the public were not involved in the design, conduct, reporting, or dissemination of this study. However, the intervention was informed by existing community dietary practices, and trial results will be shared with participants and local health authorities through community meetings and plain-language summaries.

### Trial design {12}

This is a two-arm, parallel-group, superiority, randomized controlled trial with an allocation ratio of 1:1. Participants will be randomized to receive either iron cookware for daily food preparation plus behaviour change communication package (intervention group) or standard care (control group). Control Group participants will use their usual utensils (such as aluminium or stainless steel) for daily food preparation.

## Methods: participants, interventions and outcomes

### Study setting {13}

This community-based randomized controlled trial (RCT) will be conducted in rural areas of Akola and Wardha districts in Maharashtra, India. One block from each district will be randomly selected for study. The total sample size will be equally distributed across the two sites to ensure geographic and demographic representation. Block selection in both districts will be based on the high prevalence of anemia among women of reproductive age, as reported in the National Family Health Survey (NFHS-5). On average, the prevalence of anemia in Akola and Wardha districts ranged from 54 to 59%. Both districts also represent a diverse rural population with variations in dietary patterns, socioeconomic conditions, and access to healthcare, making them suitable sites for evaluating the impact of iron pot cooking and behaviour change communication (BCC) interventions on iron status. Including two distinct rural settings will enhance the generalizability of the study findings and allow for the assessment of variations in intervention effectiveness across different populations. Randomly selecting blocks within each district will minimize selection bias and ensure a representative sample of non-pregnant, non-lactating women of reproductive age. This approach will generate evidence relevant to broader public health applications, particularly in rural India, where iron deficiency anaemia remains a major concern.

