### Participant timeline {18}

#### Sample size {19}

The sample size was calculated based on hemoglobin (Hb) as the key outcome variable. Considering a standard deviation (SD) of 1.2 g/dL and a minimum detectable difference (Δ) of 0.5 g/dL between the intervention and control groups, the required sample size was estimated to provide 80% power (*β* = 0.20) at a two-sided significance level of 5% (*α* = 0.05, 95% confidence level). The sample size was adjusted accordingly to account for an anticipated 10% attrition due to loss to follow-up, pregnancy, or withdrawal. The final required sample size is 202 participants, with 101 participants allocated to the intervention group and 101 participants to the control group [18, 19]. Since we will pool the data from two sites for the main outcome measures, the total sample size will be equally divided into two study sites.

The sampling strategy for this study involves a multi-stage approach to ensure methodological rigor and reduce potential biases. Initially, eligible villages will be purposefully selected from study areas based on predefined inclusion criteria such as population size, accessibility, and anemia prevalence data, if available. Within each selected village, a household listing will be conducted to identify households with at least one eligible non-pregnant, non-lactating (NPNL) woman of reproductive age. In instances where more than one eligible woman resides in a single household, one participant will be selected using simple random selection methods—such as a coin toss or random number generation—to prevent intra-household clustering and to maintain the independence of observations. This ensures that each household contributes only one participant to the study. Following this, the identified households will be subjected to block randomization, as previously described, to assign participants into intervention and control groups in balanced proportions. This sampling framework enables equitable group allocation, reduces selection bias, and ensures that the study sample is representative of the target population within the selected geographic context.

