### Additional analyses {27d}

Pre-specified subgroup analyses will assess effect modification by baseline anaemia status (anaemic vs non-anaemic), dietary iron intake categories, and CRP-adjusted vs unadjusted ferritin. Mixed-effects regression models will be applied with adjustment for covariates including age, body mass index (BMI), baseline iron status, dietary intake, inflammation (CRP), and socioeconomic status. Sensitivity analyses will test the robustness of results to exclusion of participants with elevated CRP, alternative adherence thresholds, and different imputation strategies. An exploratory cost-effectiveness analysis will be conducted, estimating the incremental cost per unit increase in haemoglobin (g/dL) and ferritin (µg/L).

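### Assessing variation in effectiveness is given as a reason for two sites, but no site analysis is pre-specified and the sample supports only an imprecise exploratory estimate

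*Protocol article*

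**What the plan says.** Study setting {13} takes one block from each of two districts, splits the sample equally between them and describes them as differing in diet, socioeconomic conditions and health care access. Among the reasons for two settings, it says they will "allow for the assessment of variations in intervention effectiveness across different populations".

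The other sections bearing on this are:

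- **Sample size {19}:** "The sample size was calculated based on hemoglobin (Hb) as the key outcome variable". The inputs are a "standard deviation (SD) of 1.2 g/dL and a minimum detectable difference (Δ) of 0.5 g/dL between the intervention and control groups", with 80% power at a two-sided 5% level and an "anticipated 10% attrition due to loss to follow-up, pregnancy, or withdrawal". The result is 202 women, 101 per arm. On the sites it says: "Since we will pool the data from two sites for the main outcome measures", the total is divided equally between them.
- **Primary and secondary outcomes {27a}:** continuous outcomes are analysed in a mixed model with fixed effects for group, time and their interaction. There is a random effect for participants and an optional one for clusters, which are not defined.
- **Additional analyses {27d}:** "Pre-specified subgroup analyses will assess effect modification by baseline anaemia status", dietary iron intake category and CRP-adjusted versus unadjusted ferritin. The named covariates are age, BMI, socioeconomic status, diet, CRP and baseline iron status.
- **Table 1, exploratory rows:** effect modification is listed for dietary modifiers and for baseline anaemia.

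None of these lists names site or district.

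**The concern.** The document gives a purpose for the second site and then lists its pre-specified analyses without one that serves that purpose. A comparison of the two districts would therefore be unplanned on the protocol's own terms, and nothing would mark it as exploratory. A reader of the results could not tell whether a reported site difference had been intended or was found by looking.

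The Study setting text also says nothing about precision. Without a caution there, readers may expect the trial to say more about differences between districts than 202 women can support. The interpretation of site differences is at stake, not the main result.

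**Working it through.** **Inputs** (all from Sample size {19}): SD 1.2 g/dL, difference 0.5 g/dL, 80% power, two-sided 5%, 10% attrition, equal split across two sites. Allocation is 1:1 (Trial design {12}).

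**1. Reproduce the stated sample size.**

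n per arm = 2 × [1.2 × (1.960 + 0.842) / 0.5]² = 90.4, rounded up to 91, or 182 evaluable women.

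For attrition, 91 × 1.10 = 100.1, giving 101 per arm and 202 in total, which matches the protocol. Dividing by 0.90 gives 102 per arm. The difference is immaterial here.

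**2. Standard error of the pooled effect.**

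1.2 × √(2/91) = 0.178 g/dL.

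**3. Standard error of the site-by-arm difference.** This is the difference between two site-specific arm differences, from four equal cells of N/4 women:

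SE = 1.2 × √(4 / (N/4)) = 1.2 × √(16/N).

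At N = 182 it is 0.356 g/dL, twice the pooled standard error. At N = 202 it is 0.338 g/dL.

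**4. Power, precision and detectable difference.** Power for a site difference of 0.5 g/dL is Φ(0.5/SE − 1.96). The 95% CI half-width is 1.96 × SE. The difference detectable with 80% power is 2.80 × SE.

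| Quantity | 182 evaluable | All 202 |
|---|---|---|
| SE (g/dL) | 0.356 | 0.338 |
| Power for 0.5 g/dL | 29.0% | 31.6% |
| 95% CI half-width (g/dL) | 0.70 | 0.66 |
| Detectable with 80% power (g/dL) | 1.00 | 0.95 |

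The noncentral t distribution gives 28.7% and 31.4% power, essentially the same.

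**5. Size needed for 80% power at 0.5 g/dL.**

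N = 16 × [1.2 × 2.802 / 0.5]² = 723.4, so 724 evaluable, or 805 randomised after dividing by 0.90.

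**6. Sensitivity to baseline adjustment.** The protocol gives no baseline to follow-up correlation, so this is an assumed range. With the SD multiplied by √(1 − ρ²), power (182 to 202 women) is:

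- ρ = 0.3: 31% to 34%
- ρ = 0.5: 37% to 40%
- ρ = 0.7: 50% to 55%

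All are well below 80%.

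**The case against.** The strongest reply is that the sentence is rationale for the setting and not an analysis commitment. It speaks of assessment, not of a powered test. The objectives contain no site comparison, and the sample size section says the sites are pooled. This stands, and it limits the point: 29% power is not a failed promise of power, and an estimate with its interval would meet the wording.

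A second reply is that site may be covered elsewhere. The covariate list is open-ended, the undefined clusters could be sites, and a statistical analysis plan that is not shown could add a site term. This stands in part. However, the subgroup list is worded as the pre-specified set and has no such opening. A random intercept for two sites would not estimate a site difference in effect. The planned dietary and anaemia subgroups cover some of the ways the districts may differ, but not the districts themselves.

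A reader might also infer two stronger consequences that the documents do not support:

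- **Conflicting verdicts from the two districts.** At a common true effect of 0.5 g/dL, each site alone has about 51% power, so significance in exactly one site would occur in about 2 × 0.51 × 0.49 = 50% of trials. But separate testing by site appears nowhere in the protocol, which pools.
- **A real loss of precision from omitting site.** No between-district variance is given. If the anaemia range of 54% to 59% were the two district values, with normal haemoglobin and equal SDs (assumptions), the districts would differ by about 0.13 SD. Omitting site would then add about (0.13/2)² = 0.4% to the variance, or about 0.2% to the standard error.

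**Conclusion.** The mismatch is real but minor. Variation in effectiveness across the two settings is a stated reason for the design, and no listed subgroup, fixed model term or named covariate addresses it. The sample can support an exploratory estimate of the site difference, but an imprecise one: an interval of roughly ±0.7 g/dL around a quantity whose pooled counterpart has a target of 0.5 g/dL.

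It would go too far to say that the design cannot assess variation at all, or that the plan as written leads to misleading district-level conclusions. The pooled estimate and the sample size for it stand.

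The figures assume the protocol's SD of 1.2 g/dL as the analysis SD, four equal cells, and a single haemoglobin comparison unadjusted for baseline. They concern haemoglobin because the protocol gives no SD or target difference for ferritin, which Table 1 names as the primary outcome.

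**What to change.** - **Primary and secondary outcomes {27a} and Additional analyses {27d}:** add site as a fixed effect. Pre-specify one site-by-arm interaction, labelled exploratory and reported as an estimate with a 95% CI, with no site-specific significance tests. Because the model measures the effect over time, name the visit at which this interaction is evaluated.
- **Study setting {13}:** say that the pooled effect is the trial's result and that site differences are exploratory and not powered.

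This needs no extra data, since each woman's site is known. It costs about one degree of freedom in the main model and a more modest statement about generalisability. It should be settled before any analysis by group.

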### Eligibility criteria {14a & 14b}

This will include community sensitization and enrolment. The study team will conduct awareness sessions in the community to explain the study’s objectives, potential benefits, and participation requirements. The eligibility of the participants will be assessed based on the following inclusion and exclusion criteria.

### Inclusion criteria

Women of reproductive age (18–45 years old).Non-pregnant and non-lactating at the time of enrolment.Residing in the study area for the duration of the intervention.Willingness to cook regularly at home and use the provided iron utensils.No diagnosed anemia treatment (iron supplementation or intravenous iron therapy) in the past 3 months.Participants who agreed to participate and provided informed consent for data collection (biochemical assessments, food diaries, and interviews).

### Exclusion criteria

Pregnant or lactating women at the time of enrolment.Women with chronic illnesses (e.g., kidney disease and inflammatory disorders) affectcting iron metabolism.Those with diagnosed or known haematological disorders (e.g., thalassemia, sickle cell anemia) based on haematological investigations such as CBC.Participants who will already using iron cookware regularly before the study.Severe dietary restrictions (e.g., vegan diets or food aversions preventing the consumption of iron-rich foods).Women who are on iron supplements or medications that interfere with iron absorption (e.g., proton pump inhibitors and certain antibiotics).Plans to relocate from the study area during the intervention period.

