**Methods:**

A community-based randomized controlled trial will be conducted in selected rural blocks of Akola and Wardha districts in Maharashtra, India. Eligible women (aged 18–45 years, non-pregnant, non-lactating) will be randomized into two groups: an intervention group receiving iron cookware along with structured behaviour change communication sessions, and a control group receiving non-iron cookware. Iron status indicators (hemoglobin, ferritin, serum iron, transferrin saturation, and total iron-binding capacity) will be assessed at baseline, 6 months, and 12 months after the intervention. Patient compliance with iron pot usage will be monitored through food diaries, spot checks, and interviews. Barriers and facilitators of adherence will be explored through qualitative assessments.

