### Health education and behaviour change communication (BCC) sessions

The effectiveness of cooking with iron utensils will be evaluated alongside behaviour change communication (BCC) strategies, ensuring that participants adopt and sustain cooking practices that optimize iron absorption. To reinforce knowledge and promote long-term adherence, the study team will conduct group sessions and household visits, focusing on the role of dietary iron, i.e., understanding iron-rich food sources, factors that enhance absorption (e.g., vitamin C), and dietary inhibitors (e.g., tea, coffee, phytates); Anemia Prevention and Management which includes raising awareness about the consequences of iron deficiency and the importance of routine hemoglobin checks and Sustained Behaviour Change for encouraging the habitual use of iron cookware through community-driven approaches, including storytelling and role modelling by early adopters.

Participants in the intervention group will receive fortnightly group BCC sessions for the first 3 months, followed by monthly group sessions for the next 3 months (total, 9 group sessions over 6 months). In addition, monthly individual home visit sessions will be conducted throughout the 6-month intervention period to reinforce key messages, address practical barriers, monitor cookware usage, and offer personalized support. Each group session will last approximately 45–60 min, while home visits will be of 20–30 min duration, ensuring context-specific engagement and continuous motivation.

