### Outcomes {16}

The outcome measures and assessment time points are summarized in Table 1. Blood samples will be collected at each time point for the biochemical analysis of iron status markers. Dietary intake and adherence to cookware use will be monitored using structured questionnaires and periodic household visits.

**Table 1 Tab1:** Summary of primary, secondary, and exploratory outcomes with measurement variables, analysis metrics, aggregation methods, and time points (baseline to 12 months)

Outcome type	Measurement variable	Analysis metric	Method of aggregation	Time points
Primary outcome	Serum ferritin (µg/L), CRP-adjusted	Mean change from baseline	Mean ± SD, mean difference (95% CI)	Baseline, 6 months, 12 months
Secondary outcomes	Haemoglobin (g/dL)	Mean change from baseline	Mean difference (95% CI)	Baseline, 6 months, 12 months
	Soluble transferrin receptor (mg/L)	Mean change from baseline	Mean difference (95% CI)	Baseline, 6 months, 12 months
	Transferrin saturation (%)	Mean change from baseline	Mean difference (95% CI)	Baseline, 6 months, 12 months
	Anaemia prevalence (Hb < 12 g/dL, WHO)	Proportion with anaemia	Risk difference, risk ratio (95% CI)	Baseline, 6 months, 12 months
	Nutrition knowledge and practice score	Change in score	Mean difference	Baseline, 6 months, 12 months
	Adherence to iron cookware use (≥ 1 main meal/day, ≥ 4 days/week)	Proportion adherent	Percentage adherence	Monthly monitoring; summarised at 6 months, 12 months
	Adverse events (GI symptoms, iron overload, other harms)	Proportion with ≥ 1 adverse event	Frequency counts, percentages	Ongoing; summarised at 3, 6, and 12 months
Exploratory outcomes	Cost-effectiveness (per unit Hb and ferritin increase)	Incremental cost-effectiveness ratio (ICER)	ICER	6 months, 12 months
	Dietary modifiers (vitamin C intake, tea/coffee, phytates)	Effect modification	Subgroup analyses	Baseline, 6 months, 12 months
	Subgroup analysis by baseline anaemia	Effect difference	Interaction tests	6 months, 12 months
	Community-level adoption of cookware post-trial	Proportion of households continuing usage	Adoption rate (%)	Endline at 12 months; post-trial sustainability follow-up

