### Data collection methods {25}

#### Plans for assessment and collection of outcomes {25a}

Data collection will include both quantitative and qualitative measures to evaluate iron status, dietary intake, adherence, and perceptions of the intervention. Quantitative data will be obtained through structured questionnaires to capture sociodemographic characteristics, health history, and dietary practices, as well as a 24-h dietary recall and Food Frequency Questionnaire (FFQ) to estimate dietary iron intake and food patterns. Laboratory investigations will be carried out at an NABL-accredited laboratory, where trained phlebotomists will collect blood samples for analysis of hemoglobin (Hb), serum ferritin, serum iron, soluble transferrin receptor (sTfR), transferrin saturation (TSAT), total iron binding capacity (TIBC), C-reactive protein (CRP), erythrocyte protoporphyrin, and mean corpuscular volume (MCV). These parameters will be measured at baseline, 6 months, and 12 months, with Hb and ferritin additionally assessed at 3 months. Duplicate testing will be performed on 10% of samples to ensure validity. Qualitative data will be collected through semi-structured interviews and focus group discussions (FGDs) to explore perceptions, facilitators, and barriers to cookware adoption and BCC acceptability, supplemented by field observations recorded during household visits to triangulate adherence and contextual factors. All assessors and laboratory staff will be trained and blinded to group allocation, and standard operating procedures (SOPs) will be followed at all stages to ensure consistency and data quality.

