### Missing data {27c}

Missing outcome data will be addressed using maximum likelihood estimation under the missing-at-random assumption. Multiple imputation with 20 datasets will be performed as a sensitivity analysis. Reasons for missingness (e.g., pregnancy, migration, withdrawal) will be documented. Additional sensitivity analyses will include complete-case analysis and per-protocol analysis to evaluate robustness of findings.

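### The residence and relocation criteria run only to the end of an intervention period whose one stated length is 6 months, while outcomes run to 12 months, so planned moves in months 6 to 12 are not screened out

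*Protocol article*

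**What the plan says.** Two criteria in the protocol article deal with mobility, and both refer to the intervention rather than to follow-up.

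- Inclusion criteria: "Residing in the study area for the duration of the intervention".
- Exclusion criteria: "Plans to relocate from the study area during the intervention period".

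The article puts a number on that period in one place, the section on health education and behaviour change communication: "monthly individual home visit sessions will be conducted throughout the 6-month intervention period". The group sessions described there end at the same point ("total, 9 group sessions over 6 months").

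Outcome collection goes on longer. Table 1 under Outcomes {16} lists the primary outcome, "Serum ferritin (µg/L), CRP-adjusted", at baseline, 6 and 12 months. It gives the same times for haemoglobin, soluble transferrin receptor, transferrin saturation and anaemia prevalence. Section {25a} says of the full laboratory panel: "These parameters will be measured at baseline, 6 months, and 12 months", with haemoglobin and ferritin also taken at 3 months. Table 1 summarises adherence at 12 months and places the endline for cookware adoption there too. The Discussion gives the length of follow-up as 12 months.

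The section on missing data expects some participants to move: "Reasons for missingness (e.g., pregnancy, migration, withdrawal) will be documented".

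**The concern.** Eligibility criteria on residence are there to protect the follow-up that the trial needs. Here they are tied to the intervention, and on the only stated length they stop halfway through follow-up. A woman who tells the field worker at screening that she will leave the area in month 8 satisfies both criteria and can be randomised.

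What is at stake is her 12-month data: the last ferritin and haemoglobin values, the later part of her adherence record, and the adoption outcome, whose first assessment is at the 12-month endline. The Background gives sustained use as an aim of the study, and months 6 to 12 bear most directly on it. The loss is foreseeable at screening. An analysis plan cannot repair it afterwards, because it cannot change who was enrolled.

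**Working it through.** **1. The time windows side by side**

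| Item | Runs to | Where |
|---|---|---|
| Residence requirement | End of intervention | Inclusion criteria |
| Relocation exclusion | End of intervention | Exclusion criteria |
| Intervention period, only stated length | Month 6 | Behaviour change communication sessions |
| Primary and secondary blood outcomes | Month 12 | Table 1; section {25a} |
| Adherence summary, adoption endline | Month 12 | Table 1 |

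Uncovered window: 12 − 6 = 6 months, half of follow-up.

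**2. Is 6 months the right reading?** The text does not settle it.

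- For 6 months: the behaviour change section uses the same term as the exclusion criterion and attaches a number to it. The section on ascertainment of harms lists contacts at baseline, 3, 6 and 12 months separately from the monthly visits of the intervention period, which fits a period shorter than follow-up.
- For a longer period: the cookware is for daily use with no stated end, Table 1 has monthly adherence monitoring summarised at 12 months, and the same table calls use after the 12-month endline post-trial. The participant timeline (Table 2) is a figure that is not shown.

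**3. The protocol's own sample size.** Inputs from Sample size {19}: haemoglobin SD 1.2 g/dL, difference 0.5 g/dL, two-sided 5%, power 80%, attrition 10%.

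n per arm = 2 × (1.96 + 0.842)² × 1.2² / 0.5² = 90.4

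90.4 / 0.9 = 100.5, rounded up to 101 per arm, 202 in total. The stated figure reproduces.

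**4. What planned moves could cost at 12 months.** The documents give no relocation rate, so the extra loss is an assumption. Women left per arm: m = 101 × (1 − 0.10 − extra). Power = Φ(0.5 / (1.2 × √(2/m)) − 1.96).

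| Extra loss beyond the planned 10% | Women per arm at 12 months | Power (haemoglobin) |
|---|---|---|
| 0 | 90.9 | 0.80 |
| 5 points (about 10 women in all) | 85.8 | 0.78 |
| 10 points (about 20 women in all) | 80.8 | 0.75 |

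The first row also applies if all such moves already fall within the 10% allowance, which covers loss to follow-up, pregnancy and withdrawal together and amounts to about 20 of the 202 women.

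This is a two-sample calculation at one visit, on the outcome that the protocol used for its sample size. Table 1 lists haemoglobin as secondary, and the planned analysis is a repeated-measures model. The figures therefore show the order of the effect and are not a forecast for ferritin.

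**The case against.** The strongest reply is that the gap may not exist. The 6 months appear in the section on counselling sessions and home visits, while the cookware, the main component, has no stated end. If the intervention runs to month 12, both criteria already cover follow-up. This stands as a real ambiguity. It does not dispose of the point, because field staff applying the criteria would still have only the 6-month figure to go by, and the same rewording removes the doubt on either reading.

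A second reply concerns the harm. A reader might infer that these women's primary endpoint is lost. The documents do not support that. Ferritin is also measured at 3 and 6 months, and Table 1 does not single out one time point as primary. Section {25b} commits to collecting outcomes from every randomised woman unless she withdraws consent entirely, and it provides for reminder calls and messages. The mixed model, fitted by maximum likelihood, keeps the earlier values. All of this stands. What remains is that no procedure for tracing movers is described, that migration is an expected cause of missing data, and that a likelihood analysis does not restore the 12-month information that is missing.

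Third, the 10% allowance already includes loss to follow-up, so some or all of these women may be counted in it. That also stands, and in that case the power loss shrinks or disappears.

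Finally, a reader might infer bias between the arms, or an intention to enrol women who will leave. Neither is supported. Plans held at screening precede randomisation and should balance on average, and nothing in the text suggests that movers are sought.

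**Conclusion.** The point holds as a modest and preventable weakness in two eligibility criteria. On the only stated length of the intervention period, women who already plan to move in months 6 to 12 are eligible, and their 12-month values are put at avoidable risk. The consequence is lost precision at the 12-month comparison and in the outcomes on sustained use.

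The size is uncertain. An assumed 5 to 10 points of loss beyond the planned 10% takes power on the haemoglobin calculation from about 0.80 to 0.78 or 0.75, and to the extent that the allowance absorbs these women the fall is smaller. The conclusion rests on reading the intervention period as 6 months. If it is 12 months, the criteria match follow-up, and what remains is the inconsistent statement of its length.

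**What to change.** Word the residence and relocation criteria, and the matching items on the screening form, to cover the full 12 months from randomisation to the final blood sample. Separately, state the length of the intervention period once and reconcile the behaviour change section with the 12-month adherence summary in Table 1. Compliance is defined as a share of the same period, so it too depends on that statement.

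The change is two lines of text and a form. Protocol amendments {31} calls for ethics committee approval and a registry update when eligibility changes, so it is best made before recruitment, given in Trial status as December 2025. It cannot help for women enrolled under the present wording. The downside is a few more screen failures and a slightly less mobile sample. The sample size of 202 does not change.
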